### Inclusion and exclusion criteria

#### Inclusion criteria

1. Localities require the local renal unit to share local guidance and support our interventions.

2. Primary care organisation approval for the research to be conducted in their locality.

3. Practices who provide written consent to participate.

4. Agreement to participate in whichever arm of the study they are randomly allocated.

5. Practice has had the same computer system for the last five years and has no plans to change it, and will allow access to check data quality.

6. Practice has electronic laboratory links for three years or more.

#### Exclusion criteria

1. Practices in whom the computing system has changed over the last five years.

2. Practices lacking an appropriate computer system from which data can be extracted.

3. Practices in which referral data (from primary care to secondary care) is not available.

4. Practices planning to move computer system in the next two years.

#### Consent

Practices will be asked to consent as a unit, with all GPs being willing to participate. One or more persons will sign the consent form as authorised by the practice. This may vary from all GPs to one GP being authorised to consent on behalf of the practice. No direct consent is taken from patients, however a waiting room poster is provided as well as a lay summary of the project in leaflet form.

### Interventions

#### The interventions in the study

Two interventions are being compared to usual practice: GaP and ABE. The interventions are designed to target the cluster (*i.e*., individual general practices). Where we send GaP or questionnaires we send them to individual named clinicians. Where a practice is invited to attend an ABE workshop all members may attend; however, our experience is that one or more practice members attend on behalf of the others; we try to compensate for this by providing learning resources for them to take back to their practices. However, although we send some material to individuals, the intervention is focused at the level of the practice.

##### Usual practice

These practices will be allocated to this arm at randomisation (n = 35 practices – 25 in the core CRT and 10 in the questionnaire group). Once assigned to this arm, a minimum of contacts will be made of these practices other than for data collection.

##### Distribution of clinical practice guidelines with prompts (GaP)

This is an established, low cost method of quality improvement [17]. It will provide a benchmark with which the effectiveness of the other quality improvement intervention can be compared. We will develop a consensus between the study team, our expert advisory group, and external peer reviewers, and produce appropriate guidance for the management of CKD in primary care. This guidance will be distributed to practices within this arm of the CRT (n = 25 practices plus 10 questionnaire practices) with six monthly updates and reminders. The guidance will be customised to fit with local practice and reflect guidance in that area. In addition practices will have access to a supportive website with information about CKD, frequently asked questions, and tools to improve CKD management.

The GaP documentation will typically be up to four sides of A4 paper stock, published in a glossy professionally printed form. It may be accompanied by local guidance or national brief guidance in the first intervention. We plan to distribute the NICE 'Quick Reference Guide' to managing CKD [24] as part of the second-year intervention.

##### Audit based-education (ABE)

In this arm, practices (n = 25 practices plus 10 questionnaire practices) will have a representative attend workshops. These practices will also have access to clinical practice guidelines provided to the second arm of the study. However, in addition, practices will receive three sets of detailed comparative feedback about their quality of CKD management at approximately nine-month intervals, and we will facilitate lists of patients needing interventions (local queries) being created within the practice. This comparative feedback about adherence to guidelines will be based on anonymised data collected from their general practice computer system prior to the ABE workshop.

The study will use an ABE model for quality improvement developed by the primary care data quality project that has been used in a variety of clinical contexts [19]. This involves feedback given in a workshop setting with at least one GP and one nurse or practice manager from each practice present. The workshops will be in two parts: the first will be facilitated by a GP familiar with the data, ideally from the locality, but if not, available from study team, and a local renal specialist in attendance to provide expert advice and information about local practice. The first part will be a presentation of the comparative adherence to evidence-based guidance for the management of CKD by the different practices present led by the GP. This section will highlight variation in the quality of care in a non-judgemental context. The second part of the meeting will be case studies, facilitated by the local consultant, which small groups will work through to explore dilemmas in management and how to overcome them.

The workshops are timetabled for two and a half hours of activity with additional break time to allow informal contact. Practices are expected to bring along at least one GP and one or two other members of the practice team: their practice manager and a nurse involved in cardiovascular risk assessment or diabetes within the practice.

Delegates are asked to fill in a feedback form, of the standard type used to evaluate educational meetings, on the usefulness and appropriateness of the content and the educational methods used. There is also the opportunity to provide informal feedback. This feedback, along with a narrative from the three members of the study team who participate in these workshops (it is expected there will be at least three) will be fed back into the design of subsequent feedback. Semi-structured interviews – reviewing the appropriateness of the level; the content and the delivery are being held in person or by telephone with all members of the study team who had attended or participated in the first round of workshops.

#### The content of the interventions

The content and focus of the GaP arms of the study will be the same as in the ABE arm. The areas and learning objectives for each year have been set; however, the specific details will depend on the national guidance available at the time. Currently, we are basing our year one criteria and standards on the NICE guidance released in September 2008 [4].

#### Year one

During the first year, the clinical focus will be on understanding any gap between the 'true' prevalence revealed by the audit and the 'QOF prevalence' the practice reported to the NHS Information Centre, which is publicly available information [8]. We expect our audit to identify approximately double the number of people with CKD than included in the practice QOF disease register. In addition, this year will look at proteinuria recording, control of BP and use of appropriate therapy: angiotensin modulating drugs, appendix 1.

#### Year two

The second year's clinical focus will be on the management of co-morbidities, especially diabetes. Strict control of cardiovascular risk factors in patients with CKD and Cardiovascular System (CVS) risk is important. We also look at control of BP in diabetes. People with diabetes and CKD need stricter BP control, especially if they have microalbuminuria; diabetics are also one of the most likely groups to go on to require renal replacement therapy, appendix 2.

### Outcome measures

Our primary care outcome measure is change in systolic BP in people with hypertension and stage three to five CKD. We have secondary outcome measured in the following categories:

1. What happened: Clinical outcomes and change in practitioner confidence.

2. Why change happened: Diagnostic analysis plus process evaluation.

3. What it cost: Economic evaluation.

4. Unexpected consequences.

### Primary outcome measure

The primary outcome measure is the reduction of systolic BP in hypertensive people with Stage three to five CKD towards the current national target [4]. [Hypertension is defined as above >140 mmHg in low-risk patients and >130 mmHg in high-risk patients. High-risk patients are people with CKD plus significant proteinuria (ACR ≥ 70 mg/mmol; or equivalent) or with CKD and diabetes.

We plan to measure the effect of the intervention across the same cohort, though we recognise that it will have less effect on people in stage four and five CKD, as these people are largely managed by specialists. However, as they represent a small percentage of the people with stage three to five disease (<5%) [5], we think this is unlikely to significantly distort our results. We will also explore the effect of the intervention on people older than 75 years.

### Secondary outcome measures

In addition to measuring the effect of the various quality interventions upon systolic BP, will study a number of secondary outcomes:

### Clinical and laboratory markers

1. Case definition using eGFR: We will define cases using the internationally accepted definition used by NKF Kidney Disease Outcomes Quality Initiative (KDOQI) [23], the same definition is used by NICE [4]. We will identify cases recorded since the standardisation of creatinine recording in 2006. However, we will also undertake a sensitivity analysis, including how prevalence changes when the date or number of readings are changed.

2. BP: We will measure the proportion of people in each arm with hypertension and CKD who achieve at least a ≥ 5 mmHg reduction in systolic BP. The reduction of mean systolic BP (the primary outcome measures) could be distorted in a number of ways.

3. Recording and management of key co-morbidities: diabetes and its complications; ischaemic heart disease; heart failure; obstruction/lower urinary tract symptoms.

4. Recording and management of other cardiovascular risk factors: smoking status; lipid management; proteinuria; anaemia; glycated haemoglobin and microalbuminuria in people with diabetes.

5. Serial measures of serum creatinine concentration and eGFR: to explore natural history and look for cases of accelerated decline (defined as a reduction of eGFR of >5 ml/min/1.73 m^2 ^in one year; or >10 ml/min/1. 73 m^2 ^in five years) [4].

6. Recording of death and cause of death: Although this is incompletely recorded, we will attempt to capture any recording as we expect mortality among hypertensive people over the period of the study. There may be a higher mortality among those who are in the control than intervention arms.

7. Avoiding harm: We wish to monitor whether BP reduction is associated with an increased number of falls particularly in older people. Most people with CKD are elderly and at potential risk for falls. Notwithstanding the results of recent systematic reviews that failed to show an association between falls and anti-hypertensive medication [25,26], this remains a genuine concern to some practitioners, and one that we propose to examine. A falls dataset will be devised and integrated into the renal dataset. We will investigate the relationship with use of ACE inhibitors and angiotensin II receptor blockers and systolic BP below 120 in CKD.

8. Medicines management

8. a. Use of drugs/therapy that affect renal function (for example non-steroidal anti-inflammatory drugs)

8. b. Use of ACEI and angiotensin II receptor blockers to control hypertension

8. c. Recording of medicines possession ratio based on days prescribed therapy as an index of concordance with anti-hypertensive therapy.

The details of our dataset are shown in appendix 3.

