#### Participants

The participants are GPs located in practices (our clusters) across England. We aim to recruit a nationally representative sample of practices from: in and around London – especially inner city and suburban southwest London; urban and rural Surrey and Sussex; Leicester city and surrounding areas; Birmingham inner city and suburban; and Cambridge. The locality structure is pragmatic because groups of practices need to come together for the ABE workshops. An inclusion criteria for a locality is that their local renal unit would support the workshop within their locality and review the GaP to minimise any conflict with local policy.

The primary research participants are GPs involved in the study who will receive the quality improvement interventions listed below. The interventions will be implemented at the practice (cluster) rather than the individual level. The study subjects (who may be regarded as secondary participants) will be all individuals with CKD within the study practices. CKD will be defined using the internationally accepted National Kidney Foundation (NKF) definition [23] using two measures of eGFR of less than 60 ml/min/1.73 m^2 ^at least three months apart. However, we will also explore the effects of including people with a single recording of eGFR.

The participants do not receive any financial incentives to participate, though they do receive financial compensation for the time actually spent attending study activities. These will vary according to the arm of the study they are allocated to.

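### The records that define the primary population have no cut-off at allocation, and the interventions are meant to change some of them, so the arms can differ in who is counted

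*Protocol article*

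**What the plan says.** All references are to the Protocol article.

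- **Who is studied** (Participants): "The study subjects (who may be regarded as secondary participants) will be all individuals with CKD within the study practices". CKD is established "using two measures of eGFR of less than 60 ml/min/1.73 m^2 ^at least three months apart". No reference date is given.
- **Case-finding window** (Clinical and laboratory markers, item 1): "We will identify cases recorded since the standardisation of creatinine recording in 2006". The window opens in 2006; no closing date is stated.
- **Hypertension and risk class** (Primary outcome measure): hypertension is systolic BP above 140 mmHg at low risk and above 130 mmHg at high risk. "High-risk patients are people with CKD plus significant proteinuria (ACR ≥ 70 mg/mmol; or equivalent) or with CKD and diabetes". Neither the reading nor the date that decides this is named.
- **Cohort wording** (Primary outcome measure): "We plan to measure the effect of the intervention across the same cohort". The rest of that sentence concerns the weaker effect expected in stages four and five.
- **Primary analysis** (Multivariate techniques, item 1): ANOVA of mean systolic BP in people with CKD stage three to five, by arm, before and after the interventions. No fixed list is mentioned.
- **What the interventions act on**: Objective 2 is to measure their effect on the recording, as well as the control, of proteinuria and of co-morbidities including diabetes. Under Year one, "this year will look at proteinuria recording, control of BP and use of appropriate therapy"; Year two turns to diabetes. Appendix 1, item 6, gives as an example a proteinuria test for all hypertensive patients. In the ABE arm, "we will facilitate lists of patients needing interventions (local queries) being created within the practice". Usual-practice sites have minimal contact beyond data collection.

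**The concern.** Randomising practices makes the arms comparable only for patients identified on information that allocation could not have influenced. Here the facts that admit a patient to the primary population are entries in the practice record, and two of them, proteinuria and diabetes, are entries that the active arms are encouraged to make.

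Take a person with confirmed CKD, systolic BP 136 mmHg and no ACR on record. This person is low risk, and so not hypertensive by the trial's definition. If an active-arm practice then records an ACR of 75 mg/mmol, the same person becomes high risk and hypertensive, and enters the primary population. In a usual-practice site where no ACR is requested, the person stays out. BP has not changed, but the population has.

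What is at stake is the primary comparison of systolic BP and the secondary proportion with a reduction of at least 5 mmHg. The blinded, pooled data processing does not protect against this, because the difference arises in the practices' own records before extraction.

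**Working it through.** **1. The plan's own figure.** Inputs from Sample size: SD of practice means 3.77 mmHg, difference 3 mmHg, 5% level (two-sided assumed), power 80%.

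n per arm = 2 × [3.77 × (1.960 + 0.842) / 3]² = 24.8, rounded up to 25. This reproduces the stated 25 (normal-approximation power 80.3%) and is not in dispute. It gives the yardstick used below: SE of a difference between two arms = 3.77 × √(2/25) = 1.07 mmHg.

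**2. Is each entry criterion dated, and do the interventions act on it?**

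| Criterion | Dated before allocation? | Do the interventions act on the record? |
|---|---|---|
| Two eGFRs < 60 | Start 2006, no end | Only by inference (prevalence focus, patient lists) |
| ACR ≥ 70 mg/mmol | No | Yes (Objective 2, Year one, Appendix 1 item 6) |
| Diabetes | No | Yes (Objective 2, Year two) |
| Systolic BP above 140 or 130 | No | Yes: BP control is targeted, and the threshold depends on the two rows above |

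**3. Illustration on a follow-up mean.** The documents give neither the patient-level BP distribution nor the share of new entrants, so these are assumptions. Recorded systolic BP is taken as Normal(138, 18), with 25% of values rounded to the nearest 10 and the rest to the nearest 2. By simulation:

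- mean of values above 140: 155.0; proportion above 140: 0.413
- mean of values above 130: 148.8; proportion above 130: 0.630
- mean of values above 130 and up to 140 (the entrants): 137.0

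The existing population already includes high-risk people from 130 upwards. With a share q of CKD patients already classed as high risk, its mean is

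[(1 − q) × 0.413 × 155.0 + q × 0.630 × 148.8] / [(1 − q) × 0.413 + q × 0.630].

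For q = 20% this is 153.3, a gap to the entrants of 16.3 mmHg. For q = 40% it is 151.9, a gap of 14.9 mmHg. Let f be the excess share of entrants in an active arm over usual practice. The shift in the arm mean is f × gap. With no true effect, the chance of a significant result is Φ(shift/1.07 − 1.96) + Φ(−shift/1.07 − 1.96).

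| f | Shift (mmHg) | Share of 3 mmHg | Chance of rejection |
|---|---|---|---|
| 2% | 0.30–0.33 | 10–11% | 6% |
| 5% | 0.74–0.81 | 25–27% | 11–12% |
| 10% | 1.49–1.63 | 50–54% | 29–33% |

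**4. The same entrants on a change score.** Suppose entrants do not change, existing members fall by R in every arm (for example by regression to the mean), and the active arm has a true extra fall of τ. The observed arm difference is (1 − f)(R + τ) − R = τ − f(R + τ). With τ = 3 and R = 0, f = 10% gives 2.7 mmHg instead of 3; any R above 0 takes off a further f × R. The responder proportion behaves likewise, since unchanged people add to the denominator but not to the numerator. The sign is therefore opposite to that in step 3.

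**The case against.** The strongest reply is that a closed cohort is already intended. The plan refers to one cohort, and a reduction in hypertensive people presupposes hypertension at the start. Describing subjects as everyone with CKD, and comparing before with after, are both compatible with a list fixed at baseline. The 2006 date may serve only to exclude unstandardised creatinine results, and an article may leave an index date to a fuller document.

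Part of this stands. A closed list may well be meant, and the text is undated rather than flatly contradictory. But the article does define the primary population, with an opening date and three criteria, and nothing in it ties any of them to allocation. Read as written and applied at follow-up, those rules admit people through post-allocation entries. The planned sensitivity analysis on dates and number of readings is about prevalence, and the single-eGFR exploration does not touch ACR, diabetes or BP.

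Other replies limit the point:

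- **Direction.** A reader might infer that the bias must favour ABE. The documents do not support this: the sign depends on whether a follow-up mean or a change is analysed, and entrants with higher BP could raise the mean.
- **eGFR.** A reader might infer that the prevalence work would itself create cases. The gap described lies between existing creatinine results and the QOF register, and cases are defined by eGFR results, so better register coding changes nobody's eligibility. Extra repeat testing is only an inference.
- **Progression.** A reader might extend the point to eGFR progression. That work is described as natural history, not as a contrast between arms.
- **Excess only.** QOF and NICE guidance act on all arms, and guidelines-and-prompts (GaP) content matches ABE content, so only the excess of new entries in one arm over another matters.

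**Conclusion.** The concern holds in this form: eligibility for the primary population is not fixed on pre-allocation records, the interventions are meant to change some of the records that decide it, and the cohort wording does not settle the matter. The primary comparison is therefore open to an arm-dependent difference in who is counted.

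Neither size nor direction can be taken from the documents. The range of about 0.3 to 1.6 mmHg for 2% to 10% excess entrants rests on the assumed BP distribution, on 20–40% of CKD patients already being high risk, on every entrant lying between 130 and 140 mmHg, and on existing members still having the BP distribution at which they were selected. A fall among existing members, or entrants above 140 mmHg, would narrow the gap. At the low end the effect is minor. At the high end it is about half the target difference, and later adjustment could not reliably remove it.

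**What to change.** In Participants, Primary outcome measure, Clinical and laboratory markers (item 1) and Multivariate techniques (item 1), state that the cohort is a closed list. CKD stage three to five, diabetes and proteinuria class, and hypertension are to be determined only from entries dated before the practice's own allocation. For analysis, the risk class is carried forward unchanged, whatever is recorded later.

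Base both the primary systolic BP comparison and the ≥5 mmHg responder outcome on that list. Report people who first meet the definitions after allocation separately by arm; this also serves Objective 2, for which a change in recording is a result of interest.

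The cost is mainly a date filter and some wording, since Appendix 3 already lists serial BP, creatinine and eGFR. The dates of ACR and diabetes entries would be needed as well. The downside is that cases identified after allocation leave the primary analysis.

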### Diagnostic analysis and process evaluation, including confidence and end of project questionnaires

1. Practitioner confidence to be measured at t = 0, t = 18 months using a questionnaire that assesses confidence.

2. Feedback from focus groups held prior to round one (diagnostic analysis).

3. Feedback from focus groups held mid-study and at the end of the study.

4. End of study questionnaire and workshops.

### Economic evaluation

We know the economic impact of implementing guidance in place prior to the publication of NICE guidance in September 2008 for the primary care management of CKD [27]. We will update the model used by Klebe *et al*. to reflect the restriction of investigations for renal bone disease in current guidance [4] compared with those advocated in previous guidance [28]. We will then compare the projected investigation cost with the true costs as represented in the routinely collected data.

